### Outcome assessments

For an overview of outcome assessment frequency and timing, see Fig. 1. The outcome measures listed below are consistent with the latest recommendations from the ISBD Task Force [50] suggesting the inclusion of a cognitive composite score as the primary outcome measure, a single intervention-specific cognitive measure as the secondary outcome, and multiple individual cognitive measures as tertiary (i.e. exploratory) outcome measures.

**Fig. 1 Fig1:**
[figure not shown]
Schedule of enrolment, interventions, and assessments. EPO erythropoietin, RVP Rapid Visual Information Processing (CANTAB, Cambridge Cognition Ltd.), FAST Functional Assessment Short Test, RAVLT Rey Auditory Verbal Learning Test, RBANS Repeatable Battery for the Assessment of Neuropsychological Status, WAIS-III LNS Wechsler Adult Intelligence Scale Version III Letter-Number Sequencing, OTS One Touch Stockings of Cambridge, SWM Spatial Working Memory, TMT-A Trail Making Test Part A, TMT-B Trail Making Test Part B, AQoL Assessment of Quality of Life, COBRA Cognitive Complaints in Bipolar disorder Rating Assessment, SDS Sheehan Disability Scale, UPSA-B UCSD Performance-Based Skills Assessment-B, WHOQOL-BREF World Health Organization Quality of Life, WSAS Work and Social Adjustment Scale, DART Danish Adult Reading Test, CTQ Childhood Trauma Questionnaire, SCIP Screen for Cognitive Impairment in Psychiatry (Danish version)

#### Primary outcome measures

The primary outcome measure is a cognitive composite score, consisting of neuropsychological tests covering attention, memory, and executive functions. We have previously demonstrated an improvement on this “speed of complex cognitive processing” composite measure in patients with BD after eight weeks of EPO treatment [39]. In the present trial, the specific tests included in the primary composite outcome measure are the Rey Auditory Verbal Learning Test (RAVLT) [61, 62], The Repeatable Battery for the Assessment of Neuropsychological Status (RBANS) Coding [63], Verbal Fluency with the letter “D” [64], Wechsler Adult Intelligence Scale (WAIS)-III Letter-Number Sequencing [65], Trail Making Test Part B (TMT-B) [66], and Rapid Visual Information Processing (RVP) from the Cambridge Neuropsychological Test Automated Battery (CANTAB, Cambridge Cognition Ltd.). To derive the cognitive composite score, we will z-transform and sum performance scores from RAVLT total recall, TMT-B, WAIS-III Letter-Number Sequencing, RBANS Coding, Verbal Fluency (letter “D”), and RVP speed for correct responses using the mean and SD from a healthy control group.

#### Secondary outcome measure

The secondary cognitive outcome measure consists of the RVP (CANTAB), which revealed particularly strong effects of EPO in our previous eight-week study [39], and a functional capacity outcome measure assessed with the clinician-rated interview Functional Assessment Short Test (FAST) [67].

#### Tertiary outcome measures

The tertiary cognitive outcome measure comprises the RAVLT, RBANS Coding and Digit Span, Verbal Fluency with the letters “S” and “D” [64], WAIS-III Letter-Number Sequencing, the One Touch Stockings of Cambridge (OTS; CANTAB), the Spatial Working Memory (SWM; CANTAB), as well as the TMT-B and Trail Making Test Part A (TMT-A) [66]. The tertiary level of psychosocial functioning outcome are the following questionnaires and performance-based task: Assessment of Quality of Life (AQoL) [68], the Cognitive Complaints in Bipolar Disorder Rating Assessment (COBRA) [69], Sheehan Disability Scale (SDS) [70], the UCSD Performance-Based Skills Assessment-B (UPSA-B) [71, 72], the World Health Organization Quality of Life (WHOQOL-BREF) [73], and the Work and Social Adjustment Scale (WSAS) [74]. History of early life stress will be assessed with the Childhood Abuse and Trauma Scale [75] at the time of inclusion.

To minimize learning effects on neuropsychological test performance at the follow-up assessments, alternate versions of the RAVLT (original list AB, GeAB, and Cr-AB) and RBANS Coding and Digit Span (version A and B) [61–63] are used. These versions will be administered in counter-balanced order within each stratum.

### Neural biomarkers of potential pro-cognitive effects

To assess whether an early change in neural activity in the dlPFC and mPFC is predictive of pro-cognitive efficacy, participants will complete MRI scan at baseline and following two weeks of treatment. The MRI scan duration is approximately 1.5 h and includes a structural scan, three functional tasks, including (1) a Strategic Picture Encoding Task, (2) a Verbal task, and (3) a Spatial N-back working memory task from our previous study [45], as well as a checkerboard pattern sequence and a resting state sequence. The fMRI protocol has been constructed to evaluate the sensitivity and specificity of potential neural activity change in the dlPFC and mPFC after two weeks of active treatment and whether this can predict cognitive improvement after 12 weeks of treatment.

### Exploratory measures of potential pro-cognitive effects

To further increase insight into the underlying neurobiological mechanisms involved in the potential beneficial cognitive effects of EPO, blood samples from baseline, week 3, and after treatment will be analyzed for the exploratory purpose of investigating whether baseline levels and/or changes of peripheral biomarkers, including inflammatory markers, brain-derived neurotrophic factor (BDNF), and metabolic parameters (fat and glucose markers), are correlated with cognitive improvement [76–83]. Baseline blood samples will also be used for assessment of potential influence of Catechol-O-methyltransferase (COMT: Val158Met), BDNF: Val66Met, and EPO and EPO-R genotypes on the treatment-related change in cognition and neural activity.

We will perform post-hoc exploratory analyses investigating which demographic, clinical, cognitive, and neural variables at baseline predict treatment efficacy on the primary cognitive outcome measure, since there is a paucity of research into which baseline factors are associated with cognitive improvements [84].

### Biochemistry

Research blood samples will be transferred to the Neuropsychiatric Laboratory, Rigshospitalet, and stored at − 80 °C until use. Measurements will be performed at Neuropsychiatric Laboratory, Department O, and at Department of Clinical Pharmacology, Rigshospitalet.

### Statistical analyses

The threshold for statistical significance is considered *p* < 0.05 (two-tailed). For significant results regarding the primary, secondary, and tertiary measures, relevant effect sizes will be reported in addition to the *p* values. All statistical analyses are performed using the Statistical Package for Social Sciences (SPSS, version 23, IBM Corporation, Armonk, NY, USA).

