#### Sample size and power calculation

Sample size and statistical power has been calculated by PharmaConsulting Group AB with Statistical Analysis Software (SAS), based on our previous findings assessing cognitive effects of weekly infused EPO [48]. The difference in cognitive change between the EPO and the saline-treated groups from baseline to after treatment was 0.5 SD [48]. In this trial, we estimate a clinically relevant differential change in the primary cognitive composite score between the EPO and placebo groups from baseline to week 13 (treatment completion) to be at least 0.4 SD (corresponding to a moderate effect size) with a SD of the mean change of 0.5 between these groups. This is consistent with the recommendations listed by the ISBD Cognition Task Force [50]. Specifically, the task force indicated that a differential change between groups of 0.2–0.4 SD on a global composite score reflects a potentially clinically relevant change, since this may translate into moderate–large functional improvement in patients with mood disorders [50]. In our eight-week EPO trial, the difference regarding change in the cognitive composite score from baseline to treatment completion was 0.5 SD between the EPO and the saline groups [48]. Based on the ISBD task force recommendations and our earlier findings regarding effects of longer-term EPO treatment, we estimate that a sample size of *N* = 104 (i.e. *n* = 52 participants within each sub-study with *n* = 26 in each treatment group) will reach a ≥ 80% power for detecting a similar clinically relevant differential change of 0.4 SD in the primary cognitive composite outcome measure with a SD of this change of 0.5 between the treatment groups at an alpha level of 5% (two-sided test). Based on our assumption of a 10% drop-out rate from baseline to treatment completion, we plan to recruit up to *n* = 58 for each sub-study to achieve complete datasets for *n* = 52 participants per sub-study (first-degree relatives and patients, respectively).

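### Effect sizes are promised for significant results, with no commitment for non-significant ones, so the promised effect sizes are selected on p < 0.05

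*Protocol article*

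**What the plan says.** The opening paragraph of the Statistical analyses section fixes the threshold ("The threshold for statistical significance is considered" p < 0.05, two-tailed) and then the reporting rule: "For significant results regarding the primary, secondary, and tertiary measures, relevant effect sizes will be reported" alongside the p values. The next subsection, on the primary, secondary and tertiary outcome analyses, names mixed models and intention to treat but says nothing about which estimates or intervals will be shown. No other part of the article promises an effect size or a confidence interval for a non-significant result.

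The Sample size and power calculation section judges the treatment by magnitude. Citing a task force, it says that "a differential change between groups of 0.2–0.4 SD on a global composite score reflects a potentially clinically relevant change". The design difference is stated "to be at least 0.4 SD (corresponding to a moderate effect size) with a SD of the mean change of 0.5 between these groups".

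**The concern.** The rule makes the promise of an effect size depend on the p-value, and it does so for the primary outcome as well as the exploratory ones. This has two consequences.

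- The effect sizes promised to the reader are a selected set. Those that pass p < 0.05 are on average larger than the true effect, and the smaller ones that would balance them are not promised.
- A non-significant result is where magnitude and precision matter most, because the question is then whether a difference of 0.2–0.4 SD has been ruled out. A p-value cannot answer that.

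Later syntheses that rely on the reported effect sizes would inherit the selection.

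This is not a detail that the article leaves to an analysis plan. The article chose to state a reporting rule, and the rule it states is a poor one.

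**Working it through.** **Inputs**, all from Sample size and power calculation: "52 participants within each sub-study with" 26 per treatment group; difference 0.4; change SD 0.5; two-sided alpha 5%; 10% drop-out. **Assumptions:** a two-sample t-test on change from baseline to week 13, with the 0.4 and the 0.5 on the same scale.

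**1. The plan's own figures.**
- Normal approximation: n per arm = 2 × (1.960 + 0.842)² × 0.5² / 0.4² = 24.5, so 25. Power at 26 per arm is 82.2%.
- Exact noncentral t: 26 is the smallest n per arm with at least 80% power (80.7%).
- Drop-out: 52 / 0.9 = 57.8, so 58.

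The stated sample size, power and recruitment target are reproduced.

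**2. Smallest significant difference.**
- SE = 0.5 × √(2/26) = 0.139.
- The t critical value on 50 df is 2.009.
- Threshold = 2.009 × 0.1387 = 0.279, or about 0.28.

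At the planned SD, 0.28 is also the half-width of the 95% CI.

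**3. What the filter does to the primary outcome of one sub-study.** One million trials were simulated per true effect, with 26 per arm, SD 0.5 and two-sided alpha 0.05.

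| True effect | Significant | No effect size promised | Mean estimate if significant | Ratio to truth | Mean estimate if not significant |
|---|---|---|---|---|---|
| 0.2 | 29% | 71% | 0.359 | 1.80 | 0.134 |
| 0.3 | 56% | 44% | 0.395 | 1.32 | 0.177 |
| 0.4 | 81% | 19% | 0.446 | 1.11 | 0.207 |
| 0.5 | 94% | 6% | 0.516 | 1.03 | 0.228 |

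The two groups together recover the truth. At 0.2, 0.293 × 0.359 + 0.707 × 0.134 = 0.200. At 0.4, 0.807 × 0.446 + 0.193 × 0.207 = 0.400. The distortion therefore comes from showing one group without the other, not from the estimator.

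**4. Reading a non-significant result against 0.2–0.4 SD.**
- An observed difference of 0.20 has a 95% CI of 0.20 ± 0.28, that is −0.08 to 0.48. This includes zero and the whole relevance range.
- The upper limit exceeds 0.2 for any estimate above 0.20 − 0.28 = −0.08.
- So observed differences from about −0.08 to 0.28 are non-significant and do not exclude 0.2. Those from 0.20 to about 0.27 lie inside the relevance range and would still carry no promised effect size.

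**The case against.** The strongest reply is that the sentence does not say what a reader might infer from it, namely that no estimate will appear when p ≥ 0.05. The word *only* is absent. Nothing says that group means, mean differences or model estimates will be withheld, and the mixed models committed to for all three outcome levels produce such estimates whatever the p-value. The sentence may mean no more than a supplementary standardised index for significant tests. This stands: suppression of all estimates is not supported by the text. What remains is that a promise limited to significant results makes no commitment for the others, and nothing elsewhere in the article makes one.

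The second reply concerns size. At the design effect of 0.4 the inflation is about 11%, and at the 0.5 SD reported for the earlier trial it is 3%. It reaches 1.8-fold only if the true effect is half of what was planned. The threshold of 0.28 also lies inside the plan's relevance range, so it is not true that only large differences pass. Both points stand.

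Third, significant estimates remain exaggerated on average under any reporting rule. This also stands: the fix leaves them unchanged and adds the non-significant ones, so that the full set is unselected.

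Finally, a reader might add that about 16 tertiary tests at 0.05 give 16 × 0.05 = 0.8 chance findings per sub-study and visit, each earning an effect size. That is a multiplicity count which this reporting rule neither causes nor cures. The article calls the tertiary outcomes exploratory, and most functioning measures are not collected at week 3, so the count does not apply to every visit.

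**Conclusion.** The point holds in a limited form. The protocol ties its promise of effect sizes to p < 0.05 at all three outcome levels and commits to nothing for non-significant results. Over the plan's own relevance range, a sub-study's primary result would fall outside the promise with a probability of about 19% (true 0.4 SD) to 71% (true 0.2 SD). Effect sizes reported after selection would be too large on average by a factor of 1.11 to 1.8. The main practical loss is that a null result could not be set against 0.2–0.4 SD from the promised reporting.

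The figures rest on 26 completers per arm, SD 0.5 and a t-test on change. The mixed model may be somewhat more precise, which would lower the threshold and the inflation a little. The secondary and tertiary measures were not part of the sample size calculation, so selection there cannot be quantified from the article. The validity of the primary test, alpha, power and trial conduct are not affected. The sentence should be changed, but it does not undermine the design.

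**What to change.** Replace the sentence with:

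*For every primary, secondary and tertiary measure, in both sub-studies and at each visit where it is assessed, the between-group difference from the mixed model with 95% CI and a standardised effect size will be reported regardless of statistical significance.*

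The restriction to visits where a measure is assessed is needed because the schedule does not include FAST and most functioning and quality-of-life measures at week 3. It would also help to name the standardiser: the threshold of 0.28 on the plan's scale becomes 0.28 / 0.5 = 0.56 if divided by the change SD.

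The cost is one sentence and slightly longer tables. Sample size, alpha, power and procedures do not change.

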#### Primary, secondary, and tertiary outcome measure analyses

Behavioral data from neuropsychological test score performance, subjective cognitive impairments, quality of life, level of functioning, psychosocial functioning, and mood symptoms (i.e. data from the primary, secondary, and tertiary outcomes) will be analyzed using mixed models design and intention-to-treat (ITT) analyses in cases of missing data. Data will be analyzed for every participant with any assessment. No interim analyses will be performed.

#### Functional MRI analyses

Functional MRI data are pre-processed and analyzed with FMRIB Expert Analysis Tool (FEAT) and the “randomize” algorithm implemented in FSL (FMRIB Software Library; www.fmrib.ox.ac.uk/fsl). We will assess whether early differences between EPO and placebo groups in task-related neural activity during each of the three fMRI paradigms after two weeks of treatment (adjusted for baseline activity) predict subsequent treatment efficacy on cognition at treatment completion. Neuropsychological test performance and fMRI data from 40 cognitively intact healthy controls without personal or first-degree relative history of mental illness from the BIO study [85] is used as external normative data.

Region of interest (ROI) analyses of fMRI data from the N-back working memory tasks will be carried out to investigate the effects of EPO on neural activity in dlPFC. The difference in neural activity between the EPO and saline groups in week 3 will be investigated by extracting and analyzing mean percent signal change in dlPFC adjusted for potential differences in baseline activity using univariate analysis of covariance (ANCOVA) and with whole-brain analyses (FEAT) in week 3 (with adjustment for potential activity differences at baseline). We will also investigate the hypothesized early dorsal PFC activity change in response to EPO versus saline with volume of interest (VOI) for the dorsal PFC. Volume of interest analyses of dorsal PFC and the hippocampus are conducted to assess fMRI data from the Strategic Picture Encoding Task. Finally, exploratory whole-brain analyses are conducted to assess treatment-related activity change in other brain regions. Differences in neural activity between groups will be correlated with potential change in the primary cognitive composite score at week 3 and after treatment completion. If this correlation is significant, multiple regression analyses will be performed with adjustment for mood symptoms, age, and gender to assess the potential predictive value of early neural activity change for potential pro-cognitive efficacy after 12 weeks of EPO treatment.

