
### Aims and hypotheses

The aims of the present EPO trial are threefold. First, we aim to investigate whether 12 weekly recombinant human EPO infusions ameliorate cognitive impairments in first-degree relatives without psychotic or mood disorders to patients with BD, recurrent UD, or schizophrenia (sub-study 1). This will allow for the first time to judge the disease-independent response of inherent cognitive genetic traits. Second, we will examine whether a longer treatment period is associated with similar or stronger cognitive improvement in remitted patients with BD or recurrent UD (defined as ≥ 2 treatment-requiring depressive episodes) (sub-study 2). Third, we will explore with fMRI the early neuronal changes that are predictive of subsequent clinically relevant cognitive improvement across these groups. We hypothesize that:12 weekly EPO infusions improve cognition in first-degree relatives and remitted patients with BD or recurrent UD in comparison with saline.EPO versus saline-treated participants will display early cognition-related neural activity in dorsal PFC in the direction of the activity in healthy controls, which will correlate with cognitive improvement.

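### The fMRI prediction analysis does not adjust for treatment arm, so if the arms are analysed together an EPO effect on both measures can pass for prediction

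*Protocol article*

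**What the plan says.** The third aim, in the Protocol article under Aims and hypotheses, reads: "we will explore with fMRI the early neuronal changes that are predictive of subsequent clinically relevant cognitive improvement across these groups". Two steps under Functional MRI analyses serve it.

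- Correlation: "Differences in neural activity between groups will be correlated with potential change in the primary cognitive composite score", both at week 3 and once treatment has ended.
- Conditional regression: "If this correlation is significant, multiple regression analyses will be performed with adjustment for mood symptoms, age, and gender", with the purpose "to assess the potential predictive value of early neural activity change for potential pro-cognitive efficacy after 12 weeks of EPO treatment".

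Neither step names treatment arm, an arm-by-change term or a within-arm analysis. The adjustment for baseline activity in that section belongs to the EPO-versus-saline comparison of the neural measure.

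Aims and hypotheses also states that EPO should move both quantities. For the neural measure: "EPO versus saline-treated participants will display early cognition-related neural activity in dorsal PFC in the direction of the activity in healthy controls". For cognition: "12 weekly EPO infusions improve cognition in first-degree relatives and remitted patients with BD or recurrent UD in comparison with saline".

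**The concern.** A difference between two groups is a single number and cannot be correlated with individual change scores. To be carried out, the analysis needs each participant's own neural change. If those values are taken from both arms together, randomised treatment is a common cause of the two variables. Should EPO shift both, as hypothesised, EPO participants will tend to be higher on both and saline participants lower on both, and a correlation follows from that alone. Mood, age and gender do not carry the arm difference, so adjusting for them leaves it in place.

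What is at stake is the reading of the result. The section Neural biomarkers of potential pro-cognitive effects asks whether change after two weeks can forecast cognitive improvement after 12 weeks. For an individual, that requires an association beyond the one that arm membership creates. An analysis that cannot separate the two could support a claim about individual prediction when there is none.

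**Working it through.** **Inputs.** From Sample size and power calculation: a "differential change of 0.4 SD in the primary cognitive composite outcome measure with a SD of this change of 0.5", 26 per arm, 52 per sub-study, 104 in total, 10% drop-out. From Randomization and blinding: 1:1 allocation. From Statistical analyses: two-tailed 5%. The size of the EPO effect on neural activity is not given; a standardised effect dN of 0.3 to 1.2 is assumed. The SD of 0.5 is taken as the within-arm SD of change, so the cognitive effect is dC = 0.4/0.5 = 0.8.

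**The plan's own figures first.** The normal approximation gives 2 × (1.96 + 0.842)² / 0.8² = 24.5, so 25 per arm for 80% power. At 26 per arm, power is 82.2% (normal) or 80.7% (noncentral t). Recruitment is 52 / 0.9 = 57.8, so 58. All agree with the document. It states no figure for the fMRI correlation or regression.

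**Correlation caused by arm alone.** Set the within-arm correlation to zero. With 1:1 allocation, the covariance that arm creates is dC × dN / 4, and the total variances are 1 + dC²/4 and 1 + dN²/4 in within-arm SD units. Hence

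r = (dC × dN / 4) / √[(1 + dC²/4)(1 + dN²/4)].

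For dN = 0.8: r = 0.16 / 1.16 = 0.138. For dN = 0.3: r = 0.06 / √(1.16 × 1.0225) = 0.055. For dN = 1.2: r = 0.24 / √(1.16 × 1.36) = 0.191.

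**How often each step is significant.** Simulation with 40,000 runs per cell, dC = 0.8, no within-arm association, and mood, age and gender unrelated to either measure. Each cell gives n = 52 / n = 104.

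| Assumed dN | Induced r | Correlation, p < 0.05 | Planned regression, no arm | Same regression plus arm |
|---|---|---|---|---|
| 0 | 0 | 5.0% / 4.9% | 5.1% / 4.9% | 5.0% / 5.0% |
| 0.3 | 0.055 | 7.0% / 8.4% | 7.0% / 8.4% | 5.2% / 5.1% |
| 0.5 | 0.090 | 9.7% / 14.8% | 9.4% / 14.3% | 5.1% / 4.9% |
| 0.8 | 0.138 | 16.1% / 28.8% | 15.5% / 28.3% | 5.0% / 4.8% |
| 1.0 | 0.166 | 21.8% / 40.1% | 20.8% / 39.0% | 4.8% / 4.9% |
| 1.2 | 0.191 | 28.0% / 50.4% | 26.6% / 49.3% | 5.0% / 5.2% |

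The regression columns are for the model fitted in every run.

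**What the significance condition does.** It does not create the bias: with dN = 0 the correlation is significant in about 5% of runs. It does make the regression close to redundant. Over dN = 0.3 to 1.2, once the correlation is significant, the planned regression is significant too in 80% to 94% of runs, so it is not an independent check. Keeping the condition would also spoil the repaired model. At n = 52, among runs where the correlation was significant, the neural term adjusted for arm is still significant in 43.3% (dN = 0.3) falling to 9.2% (dN = 1.2), because those runs were selected for a strong sample association.

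**The case against.** **Pooling of the arms is not stated.** The regression's purpose speaks of efficacy after EPO treatment, which could mean the EPO arm alone, and that analysis would not be confounded by arm. A reader might infer that the protocol commits itself to a pooled analysis; it does not. This stands, and the conclusion is conditional on it. Pooling remains the natural reading: the correlation sentence refers to differences between groups, and the same section frames the question as whether EPO-placebo differences in activity predict later efficacy. Nor is this mere silence left to an analysis plan, since the covariates are listed and arm is not among them.

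**The biomarker is partly a tool for screening treatments.** Background and Perspectives describe a model for detecting efficacy and prefrontal target engagement. For that purpose the shift caused by treatment is part of the signal, and adjusting for arm removes it. This also stands. A reader might infer that a pooled correlation is worthless; the document does not support that. It is informative about treatment acting on both measures, but it does not show that individuals with more neural change improve more.

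**The size depends on an assumption.** With a small neural effect the inflation at n = 52 is modest (7.0% and 9.7% for dN = 0.3 and 0.5). A reader might infer rates near 30% at n = 52 and 53% at n = 104 by setting both effects to 1.0, but the protocol's cognitive effect is 0.8. Participants who cannot be scanned stay in the trial without fMRI (Participants), so the scanned numbers may fall short of 52 and 104, where inflation would be smaller.

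**The significance condition is a lesser matter.** A reader might infer that it costs power, since a true correlation of 0.3 reaches significance in only 53% to 58% of trials at n = 46 to 52. That is simply the power of a correlation test at those sizes; removing the condition does not change it.

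**The analysis is exploratory.** The third aim says so, and fMRI is not among the primary, secondary or tertiary outcomes. This limits the weight of the point but does not remove it, because this is one of three stated aims.

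**Conclusion.** The point holds in conditional form. If both arms enter the correlation and regression together, omitting arm lets an EPO effect on both measures appear as prediction. With the protocol's cognitive effect of 0.8 and an assumed neural effect of 0.3 to 1.2, the correlation is significant in about 7% to 28% of trials at n = 52, instead of 5%, with no within-arm association at all. At n = 104 the range is about 8% to 50%, but pooling the sub-studies is a further assumption: the third aim's wording makes it plausible without stating it. The figures use the week-13 effect; the document gives none for cognition at week 3. The omission of arm causes the problem; the significance condition only adds selection. Conclusions on primary efficacy are not touched. The change is worth making because it is nearly free and settles what a positive biomarker result would mean.

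**What to change.** In Functional MRI analyses:

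1. State that the neural variable is each participant's week-3 minus baseline dPFC change, and say whether arms and sub-studies are analysed together.
2. Add treatment arm to the planned mood, age and gender covariates, and add sub-study if the two are pooled.
3. Fit this regression whatever the p-value of the correlation.
4. Base individual-level predictive claims on the arm-adjusted slope from the model without an interaction. Report within-arm slopes and an arm-by-change term, with neural change centred, as supportive only; with about 26 per arm the interaction will be imprecise.
5. The pooled correlation may still be reported, described as reflecting the treatment effect on both measures.

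If an EPO-arm-only analysis is intended, say so; arm adjustment is then unnecessary.

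The cost is one or two extra model terms and a slope that may be slightly less precise, in an exploratory analysis. No new data are needed.
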